#### Primary outcome

2.10.1

The primary outcome is the incidence of moderate-to-severe pain at 24 h postoperatively. APSP is common after VATS, often peaking within 24–48 h (32). Pain can inhibit breathing leading to atelectasis and impair postoperative mobility and physiotherapy (33). Pain intensity will be recorded using the Numerical Rating Scale (NRS) (34). An NRS score ≥ 4 is defined as moderate-to-severe pain (35). The primary outcome measure will be the NRS score for the most severe pain experienced within 24 h, recorded prior to any rescue analgesic administration.

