#### Secondary outcomes

2.10.2

The postoperative period is defined as starting from the time of PACU admission.

(1).Time to first PCIA demand (from surgery end to first effective PCA button press with drug delivery).(2).Resting pain scores (NRS) at 2 h (T1), 6 h (T2), 12 h (T3), 24 h (T4), 48 h (T5), and 90 days (T6) postoperatively. Resting pain is assessed while the patient is lying quietly.(3).Movement pain scores (NRS) at T1–T6 postoperatively. Movement pain is assessed during turning or coughing.(4).PACU length of stay (hours from PACU admission to discharge).(5).Area under the curve (AUC) for resting pain scores from T1 to T5 (0–48 h), calculated using the trapezoidal rule, to quantify total pain burden.(6).AUC for movement pain scores from T1 to T5 (0–48 h), calculated using the trapezoidal rule.(7).Quality of Recovery assessed by QoR-15 score at 24 h (T4) and 48 h (T5) postoperatively.(8).Extubation time (minutes from cessation of all maintenance anesthetics to safe removal of the endotracheal tube). The decision to extubate, made by a blinded anesthesiologist, will be based on standard clinical criteria.(9).Record the dosage of rescue analgesics administered within 48 h postoperatively, expressed in milligram equivalents of oral morphine (MME). Rescue analgesia is administered according to the protocol if the patient’s resting pain numerical rating scale (NRS) score is ≥4 within 48 h postoperatively. For standardized comparison, all opioid medications are converted to milligram equivalents of oral morphine based on the American Academy of Pain Medicine guidelines (36).

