### Sample size calculation

2.13

Our preliminary findings indicate a 70% incidence of moderate-to-severe pain postoperatively. Given prior studies reporting analgesic effects of rTMS over the M1 region, we hypothesize that a reduction in moderate-to-severe pain incidence to 50% following two interventions would constitute an effective therapeutic response (37). With α = 0.05 and β = 0.2 (80% power), the required sample size is 103 per group. Considering a 10% dropout rate and future subgroup analyses, we aim to recruit 260 patients, randomly assigned to active and sham stimulation groups.

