### Statistical analysis

2.14

Analysis will follow the intention-to-treat (ITT) principle using SPSS 27.0, with graphs created in GraphPad Prism 8.0. The Kolmogorov-Smirnov test will check normality, and Levene’s test will evaluate variance homogeneity. Data will be presented as mean ± standard deviation for normal distributions and median with interquartile range for non-normal distributions.

Continuous variables will be assessed with the *t*-test or Mann-Whitney U test, depending on distribution. Categorical variables, including the primary outcome, will be examined using chi-square tests or Fisher’s exact test, with differences shown as relative risk and 95% CI. Comparisons of primary outcomes used generalized estimating equations (GEE). The interaction between treatment and time was first assessed. If this interaction was statistically significant, Bonferroni-corrected multiple comparisons were performed to assess differences between groups at each individual time point. If not, the primary treatment effect was then assessed at each time point without applying the Bonferroni correction. For other replicated measurement data, GEE were similarly employed for analysis. Multivariate analysis will use linear or logistic regression models based on the outcome type. Missing data will be addressed with multiple imputation, and a per-protocol analysis will be included for sensitivity. Benjamini-Hochberg correction for secondary outcomes. A significance level of α = 0.05 will be applied, with *p* < 0.05 deemed significant.

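### Keeping the 90-day pain score in the same GEE series as the 2–48 h scores lets a faded acute effect trigger the Bonferroni penalty on the acute time-point comparisons

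*Protocol article*

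**What the plan says.** Section 2.10.2 of the protocol article defines resting NRS at 2, 6, 12, 24 and 48 h and at 90 days as one secondary outcome. It does the same for movement: "Movement pain scores (NRS) at T1–T6 postoperatively". Table 1 schedules both scores at all six times.

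Section 2.14 describes a two-step GEE analysis that begins with the treatment-by-time interaction. "If this interaction was statistically significant, Bonferroni-corrected multiple comparisons were performed to assess differences between groups at each individual time point". If the interaction is not significant, each time point is tested without that correction. The approach is then extended: "For other replicated measurement data, GEE were similarly employed for analysis". The two NRS series are the plainest examples of such data. Secondary outcomes also receive a Benjamini-Hochberg correction; how this combines with the Bonferroni step is not stated.

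No section removes T6 from the NRS models or gives it its own analysis. The two AUC outcomes in section 2.10.2, by contrast, stop at T5 (48 h).

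**The concern.** Five of the six measurements fall within two days of surgery and the sixth comes three months later. The hypothesis in the Introduction is about attenuating acute pain, and section 2.10.1 places that pain early: "APSP is common after VATS, often peaking within 24–48 h". If the treatment helps over 2–48 h and the difference is smaller or gone at 90 days, the effect differs between time points, and that is what the interaction test detects. The test then responds to the contrast between the acute period and day 90, even when the effect is constant across the whole acute period.

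The consequence is a stricter threshold for the acute comparisons, 0.05/6 instead of 0.05. It is applied because of a score that says little about acute pain. The larger the true acute benefit, the more likely this becomes. Rewording what follows from a significant or non-significant interaction would not cure it, because T6 would still drive the test.

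**Working it through.** **Numbers analysed.** The plan's own figure comes first. Section 2.13 states: "With α = 0.05 and β = 0.2 (80% power), the required sample size is 103 per group", for 70% versus 50%. Two-sided, n = [1.960·√(2·0.6·0.4) + 0.8416·√(0.7·0.3 + 0.5·0.5)]² / 0.2² = 93.0. With the continuity correction, (93.0/4)·[1 + √(1 + 4/(93.0·0.2))]² = 102.8, so 103 per group. The stated figure reproduces. The planned 260 gives 130 per arm, or 130 × 0.9 = 117 after the stated 10% dropout.

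**Assumptions.** The documents give no NRS SD, correlation or effect size. Assumed: SD 2 at T1–T5 and 1.5 at T6; correlation ρ = 0.4–0.6 among T1–T5 and 0.2 between each of these and T6; a constant benefit D at T1–T5 and none at T6.

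**Chance that the interaction is significant.** With a constant acute effect, the Wald interaction test has noncentrality λ = D²/v on 5 df, where v = (2/117)·[4(1 + 4ρ)/5 + 1.5² − 2·0.2·2·1.5].

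- ρ = 0.4: v = (2/117)·(2.08 + 2.25 − 1.20) = 0.0535. For D = 0.8, λ = 0.64/0.0535 = 11.96.
- ρ = 0.6: v = (2/117)·(2.72 + 2.25 − 1.20) = 0.0644. For D = 0.8, λ = 0.64/0.0644 = 9.93.

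The probability of exceeding the 5% critical value of 11.07 is:

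| Constant acute benefit (points) | T1–T6 in the model | T1–T5 only |
|---|---|---|
| 0.4 | 19–22% | 5% |
| 0.6 | 40–48% | 5% |
| 0.8 | 67–77% | 5% |

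Only the difference between the acute and 90-day effects enters λ. A 0.8-point acute benefit with 0.2 points remaining at T6 therefore also gives 40–48%.

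**Cost once triggered.** The standard error at one acute time point is √(2·2²/117) = 0.2615. For 0.8 points, 0.8/0.2615 = 3.059.

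- At 0.05: 3.059 − 1.960 = 1.099, power 86%.
- At 0.05/6 = 0.0083: 3.059 − 2.638 = 0.421, power 66%.
- At 0.05/5 = 0.01: 3.059 − 2.576 = 0.483, power 69%.

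For 0.6 points, power is 63% at 0.05 and 37% at 0.05/6. Going from six comparisons to five therefore gains only about 2 points. Most of the loss comes from the Bonferroni branch being entered at all.

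**Wider range.** A second set of assumptions used standardised acute effects of 0.2 to 0.524, where 0.524 is the latent-normal equivalent of 70% versus 50%. Correlation within T1–T5 was 0.3–0.7, T6 correlation was 0.1 or that same value, the T6 SD was 0.6–1.0 times the acute SD, and there were 117 or 130 per arm. The probability of a significant interaction was 0.13–0.64 at effect 0.2 and 0.69–1.00 at 0.524. At 0.524 with 117 per arm, power per time point falls only from 98% to 92%.

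**If the effect also fades within 48 h.** With assumed multipliers 1, 1, 0.9, 0.8 and 0.5 of 0.524 over T1–T5 (T6 SD ratio 0.8, T6 correlation 0.1), the interaction is significant with probability 0.89–0.96 with T6 and 0.32–0.73 without it.

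**What is untouched.** The trapezoidal AUC over 2–48 h weights T1–T5 by 2, 5, 9, 18 and 12 (sum 46). Under the first set of assumptions at 0.8 points, its standard error is 0.196–0.220 on the NRS scale and its power at 0.05 is 95–98%, with no interaction test involved.

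**The case against.** The strongest reply is that the interaction test would be doing its job. If the benefit is real to 48 h and gone at 90 days, the effect does vary over the series analysed, and correcting six comparisons is ordinary multiplicity control. Much of the contrast between 86% and 66% is simply uncorrected against corrected testing, and neither figure includes the Benjamini-Hochberg step. This stands as a limit on the size. It does not explain why a 90-day score should decide how the acute comparisons are corrected.

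T6's place in the model is also inferred, since section 2.14 lists no time points and the article may condense a fuller plan. The inference follows from Table 1, section 2.10.2 and the wording of section 2.14, and nothing contradicts it.

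Three stronger readings are tempting, but the documents do not support them:

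- **A missed interaction would leave a pooled effect diluted by the 90-day score.** Section 2.14 specifies no pooled effect. Its non-significant branch tests each time point separately and without Bonferroni.
- **The acute-pain question as a whole is answered worse than the data allow.** The AUC outcomes already address overall burden over T1–T5, exclude T6 and face no interaction test.
- **The documents treat pain at 90 days as a separate condition, so the benefit must shrink there.** The Discussion says acute pain may develop into chronic pain, and the Introduction calls severe acute pain a strong predictor of it. A 90-day effect is conceivable. That it is smaller or absent is an assumption here.

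**Conclusion.** The point holds for the secondary per-time-point NRS comparisons and no further. As written, an acute effect that is smaller or absent at 90 days can by itself move the acute comparisons to 0.05/6. Under the first set of assumptions this happens about 19–22%, 40–48% or 67–77% of the time for a constant benefit of 0.4, 0.6 or 0.8 points, against 5% without T6. At 0.8 points the threshold change takes power per time point from 86% to 66%.

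These figures rest on assumed SDs, correlations and effects. The 5% comparator needs an effect that is constant over 2–48 h; one that fades within 48 h can trigger the correction without T6, so removing T6 reduces the problem but does not abolish it. A reader might infer that the main result or the sample size is at risk. Neither is: both rest on a binary outcome at 24 h, which has no 90-day component. This is a worthwhile, inexpensive improvement to the secondary analysis.

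**What to change.** In section 2.14, state that the GEE and its treatment-by-time test for resting and movement NRS use T1–T5 only, the 48 h boundary already set for the AUC outcomes. State that 90-day NRS is analysed as a separate secondary between-group comparison for each pain state, within the Benjamini-Hochberg family. The change should be made before unblinding.

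The cost is a change of wording and one extra comparison per pain state in that family. No further patients or data are needed.

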## Discussion

3

Video-assisted thoracoscopic surgery remains a primary therapeutic approach in thoracic surgery. Compared to open procedures, it offers significant advantages, including smaller incisions, reduced morbidity, accelerated recovery, diminished postoperative pain, and shorter hospital stays (38). However, VATS can lead to severe APSP that may develop into chronic pain lasting over 3 months (39). This type of pain is typically neuropathic and may manifest as referred pain in other parts of the body (40, 41). Postoperative pain following VATS represents a multifactorial and complex condition. It extends beyond minor incisional discomfort and results from the combined effects of chest tube irritation, nerve injury, manipulation of deep tissues, and musculoskeletal retraction (42). Furthermore, perioperative exposure to high-dose opioids may induce acute opioid tolerance and potentially opioid-induced hyperalgesia, while also altering the balance of descending inhibitory and facilitatory pathways originating from higher brain centers (43). Consequently, postoperative analgesia for VATS has emerged as a critical focus in the fields of anesthesiology and clinical surgery. Currently, the commonly employed postoperative analgesic modalities primarily include regional nerve blockade techniques, regional analgesic infusion techniques, and pharmacologic adjuncts. In regional nerve block techniques, the vertical erector spinae plane block is preferred over classic paravertebral and intercostal blocks because it is safer and less likely to harm critical structures. This technique is particularly suitable for patients undergoing anticoagulant therapy (44). New techniques such as the posterior superior serratus plane block are also undergoing clinical trials to validate their efficacy, offering physicians additional treatment options (45). For regional analgesia techniques involving indwelling catheters, the programmed intermittent epidural bolus (PIEB) modality demonstrates distinct advantages over traditional continuous infusion. By delivering anesthetic in a pulsed manner, PIEB facilitates more effective diffusion of the local anesthetic, resulting in a broader sensory block range and, to some extent, a reduction in overall drug consumption (46). Liposomal bupivacaine, a long-acting local anesthetic, provides sustained and more stable analgesia for up to 72 h when used for intercostal nerve blockade, effectively reducing patient pain scores. Adding intravenous dexamethasone and dexmedetomidine to nerve blocks reduces postoperative pain, opioid use, nausea, and vomiting, while improving recovery quality within 24–48 h (47). Virtual reality (VR) technology, as an innovative adjunct analgesic method, effectively distracts patients from pain and modulates pain perception by immersing them in virtual environments combined with cognitive behavioral therapy and breathing exercises. Studies indicate that combined VR analgesia significantly improves NRS scores within 48 h post-surgery (48). No single analgesic method is flawless, so multimodal analgesia is considered the gold standard.

Transcranial magnetic stimulation (TMS) is a safe, non-invasive technique that uses a changing magnetic field to create electrical currents in targeted brain areas, like the primary motor cortex, to alter neuron excitability. Due to its transient effects, a single session of TMS lacks clinical utility. rTMS involves the application of repetitive and rhythmic pulse stimuli to a specific brain region over an extended period, utilizing a fixed frequency and pattern (49). Currently, rTMS has become a relatively mature therapeutic approach in the treatment of neurological disorders and psychiatric conditions (50, 51). rTMS can cause long-term potentiation or depression, helping to reshape brain networks and showing promise in treating chronic pain. A 2015 meta-analysis found that high-frequency rTMS effectively reduces neuropathic pain, with multiple sessions enhancing its therapeutic impact (52). Research suggests that rTMS is a promising alternative to traditional drug therapy for managing pain in patients with various non-CNS cancers, including breast, non-small cell lung, gynecological cancers, multiple myeloma, and cellular glioma (53). A meta-analysis of 1,158 patients found that rTMS significantly reduced depression scores and enhanced follow-up outcomes and quality of life in those with musculoskeletal pain (54). Zhong et al. demonstrated that neural modulation through rTMS is significantly correlated with the alleviation of chronic phantom limb pain (55). Further research indicates that stimulating the dorsolateral prefrontal cortex (DLPFC) can also produce a measurable analgesic effect (56). The DLPFC is a crucial component of the prefrontal cortex. Rather than directly processing the physical signals of pain, it functions as the brain’s higher-order command center, deeply involved in cognitive control, emotional regulation, and attention allocation. By regulating the emotional and affective dimensions of pain, it indirectly suppresses excessive negative emotional responses in downstream limbic systems, thereby alleviating the emotional distress associated with pain (57). Studies have demonstrated that stimulating the DLPFC with rTMS can prevent migraine attacks (58). The findings of Che et al. provide evidence that high-frequency stimulation of the DLPFC can elicit analgesic effects in both chronic pain conditions and in response to experimentally induced pain (59). In summary, rTMS demonstrates considerable potential in alleviating chronic pain.

The feasibility of rTMS in alleviating APSP has recently emerged as a research focus. The theoretical basis for this lies in the fact that the conscious perception of pain is ultimately integrated by the cerebral cortex. High-frequency stimulation of key pain matrix nodes, like the M1 area, through rTMS can activate natural pain relief pathways and alter brain activity in regions like the anterior cingulate cortex and insula, disrupting acute pain signal processing. rTMS enhances the excitability of cortical neurons over the long term, strengthens the cortical structures involved in descending pain inhibition, and suppresses central sensitization, thereby reducing patients’ perception of pain. This provides a theoretical basis for the preventive use of rTMS to alleviate postoperative pain (60). Animal experiments have shown that rTMS can increase the levels of brain-derived neurotrophic factor in the prefrontal cortex, which helps promote neuroplasticity and allows the brain to adapt and respond to upcoming pain stimuli in a healthier manner (61). Compared to traditional pharmacologic analgesic approaches, rTMS offers unique advantages including the absence of systemic side effects, no drug-drug interactions, and high patient acceptance. Although this field is still in its exploratory stages and requires more large-scale randomized controlled trials to optimize stimulation protocols and confirm the durability of its efficacy, preliminary clinical evidence suggests that administering a single session or a short course of rTMS treatment to patients, either before or after surgery, holds promise as an effective adjunct analgesic modality. This approach provides a new non-drug option for creating multimodal postoperative pain relief plans (62–64).

The NRS is a widely used pain assessment tool with a 0–10 scale, where 0 indicates no pain and 10 indicates the worst possible pain (65). In this study, pain with an NRS score of 4 or higher was considered moderate to severe. Reports indicate that 50%–70% of patients experience such pain within 24–48 h after surgery. Thus, the occurrence of moderate-to-severe pain at 24 h post-surgery is a suitable primary outcome measure for this study (66). As no previous studies have explored rTMS’s impact on APSP, we based our stimulation parameters on preclinical findings from standard rTMS research (67). A meta-analysis of rTMS and pain-related research indicated that 12 out of 15 studies targeted the primary motor cortex (68). In clinical studies, high-frequency stimulation (10 Hz) rTMS is used for pain treatment, typically at 80%–90% RMT (69, 70). For safety and efficacy, we chose a 10 Hz, 3,000-pulse stimulation protocol for the M1 region (71).

There are several limitations to note: the study’s single-center nature and modest sample size may limit generalizability; the limited range of VATS procedures at our institution might restrict broader applicability; fixed stimulation parameters were used without exploring dose-response relationships; and objective biomarkers for postoperative pain recovery were not included.

While preclinical research on rTMS for perioperative pain relief is developing, clinical evidence is still scarce. This study examines the effects of this non-invasive technique on APSP in VATS patients, offering a new angle on multimodal pain management and potentially enhancing postoperative recovery.
